### Outcomes

The primary and secondary outcomes, as well as descriptive variables, are shown in Table 2. All primary outcomes will be assessed at participants' homes, whereas some secondary outcomes and descriptive variables are recorded at the end of inpatient rehabilitation.

**Table 2 Tab2:** Overview of the primary and secondary outcome measures, descriptive variables, and date of data collection

	**Variables**	**T**_**0a**_	**T**_**0b**_	**IA**^**a**^	**T**_**1**_	**IA**^**b**^	**T**_**2**_
**Sociodemographics**							
D	Age, sex, education, living conditions	x					
**Medical information & comorbidity**							
D	Diagnosis relevant for rehabilitation	x					
D	Cumulative Illness Rating Scale-Geriatric [35]	x					
D	Pain		x		x		x
D	Intercurrent medical events (diseases, accidents)		x	x^a^	x	x^b^	x
D	Medication (type, dosage, frequency)		x		x		x
**Health-related quality of life and resource use**							
S	EuroQol-5-Dimension 5-Level [36]		x		x		x
S	Adapted version of the questionnaire for the use of medical and non-medical services in old age (FIMA) [37]				x		x
**Information on general physical health condition, body weight, and nutritional & gastrointestinal status**							
S	Simplified Nutrition Appetite Questionnaire [38]	x	x	x	x		x
S	Mini Nutritional Assessment—short form [39]		x		x		x
D	Global Leadership Initiative on Malnutrition criteria [40]	x					
D	Subjective Global Assessment [41]	x					
**Anthropometric data**							
D	Body weight	x	x		x		x
D	Ulnar length		x				
D	Arm circumference		x		x		x
**Frailty**							
S	Groningen Frailty Indicator [42]		x		x		x
S	Clinical Frailty Scale [43]		x		x		x
**Neuropsychological status**							
D	Trail Making Test (A & B) [44]		x				
**Falls, concerns about falling, and management of falls**							
S	Falls Efficacy Scale International - short form [45]		x		x		x
S	Perceived Ability to Manage Falls [46]		x		x		x
S	Number of falls		x	x^a^	x	x^b^	x
**Social participation, mobility, physical capacity, and activity**							
P, S	Modified Reintegration to Normal Living Index [47]		x		x		x
S	Late-Life Function and Disability Instrument – short form (disability component) [48, 49]		x		x		x
S	Life-Space Assessment for Persons with Cognitive Impairment [50, 51]		x		x		x
P, S	Short Physical Performance Battery [52]		x		x		x
S	Handgrip strength [53]		x		x		x
S	Physical activity assessed with body-worn sensors		x		x		x
**Goal attainment and training adherence (only in intervention groups)**							
D	Goal Attainment Scale [54]				x		
D	Training diary				x		x
**Technology experiences**							
D	Experience with the use of smartphones, tablets, or laptops		x				
D	Mobile Device Proficiency Questionnaire-16 [55]		x				
D	System Usability Scale [56]				x^c^		

*Abbreviations*: *P* Primary outcome measure, S Secondary outcome measure, D Descriptive measure, T_0a_ Assessment by clinical physician, T_0b_ Baseline assessment, T_1_ 3-month assessment, T_2_ 6-month assessment, IA Interim assessment (^a^ within the intervention period, ^b^ within the follow-up period)

^a^recorded once a week, ^b^recorded once a month, ^c^only in the tablet intervention group

The assessments will be distinguished as follows: T0a = assessment by a physician (1–5 days before discharge), T0b = baseline assessment (2–6 working days after discharge), T1 = three-month post-assessment (13 ± 1 week[s] after discharge), and T2 = six-month follow-up-assessment (26 ± 2 weeks after discharge).

#### Primary outcomes

The primary outcome measures will be the physical capacity measured by the Short Physical Performance Battery (SPPB) and the social participation assessed by the modified Reintegration to Normal Living Index (mRNLI), 3 months after discharge (T1).

The SPPB is an objective assessment tool for evaluating lower extremity function in older persons including static balance, gait speed, and repeated chair rises [52]. It is considered a "gold standard" for evaluating exercise interventions in older persons, as the result is highly predictive for disability, rehospitalization, institutionalization, and mortality [57–60], and therefore a good indicator for future loss of autonomy.

The mRNLI is an instrument that incorporates social, psychological, and physical aspects and assesses patients’ perceptions of their ability to resume activities of daily living after a disabling illness or injury [47]. This 11-item questionnaire consists of two subscales. Information about regular activities, including questions about mobility, ability for self-care, daily activities, leisure activities, social activities, and family roles, is summarized in the subscale “Daily Functioning”. Interpersonal and intrapersonal behaviors, represented by questions on personal relationships, self-presentation, and general coping skills, are summarized in the subscale “Personal Integration”. All items of the mRNLI are rated on a 4-point Likert-scale (0 points = does not describe me or my situation; 1 point = sometimes describes me or my situation; 2 points = mostly describes me or my situation; 3 points = fully describes me or my situation). The mRNLI has demonstrated validity in studies of community integration of persons living with long-term consequences of chronic health conditions [61] and has been validated in pre-frail to frail older persons living in the community [62].

#### Secondary outcomes

Lower extremity function, assessed with the SPPB, and the self-perception of the ability to resume activities of daily living after the inpatient rehabilitation, measured with the mRNLI, will also be considered as secondary outcomes at the end of the follow-up period (T2).

Concerns about falling during social and physical activities will be assessed with the short form of the Falls Efficacy Scale International (short FES-I) [45]. Elements of self-efficacy independent of physical activities and the ability to cope with falls will be assessed with the Perceived Ability to Manage Falls scale (PAMF) [46].

Frailty will be assessed by a self-assessment instrument (Groningen Frailty Indicator; GFI) [42] as well as the Clinical Frailty Scale (CFS) rated by assessors [43].

Information on the frequency of participation in particular activities and the associated limitations on engaging in those activities will be measured with the disability component of the Late-Life Functional and Disability Instrument (LLFDI) [48, 49].

The Life-Space Assessment in Persons with Cognitive Impairment (LSA-CI) will be used to assess the participants’ life-space mobility. The LSA-CI is an instrument to assess life-space mobility of the previous week by the frequency of movements and assistance needed to reach the individual activity area [50, 51].

Physical activity will be objectively recorded over 7 days using a 6-axis inertial measurement unit (AX6, Axivity Ltd., Newcastle, UK) fixed at the lower back. Handgrip strength will be measured with a JAMAR digital hand dynamometer following a standardized protocol [53].

The participants' appetite will be determined by using the Short Nutritional Appetite Questionnaire (SNAQ). This four-item questionnaire is a validated and reliable instrument, which is easy to use in older adults [38]. The nutritional status will be assessed with the short form of the Mini Nutritional Assessment (MNA-sf), a validated assessment tool to detect malnutrition in geriatric patients [39]. On discharge from inpatient rehabilitation, malnutrition will be diagnosed according to the Global Leadership Initiative on Malnutrition (GLIM) criteria as well as by the Subjective Global Assessment [40, 41].

To quantify the participants’ health-related quality of life, the 5-level version of the EuroQol-5-Dimension questionnaire (EQ-5D-5L), including a visual analog scale to quantify subjective overall health, will be used [36].

Pain at rest and while walking or standing will be assessed using a 5-point verbal rating scale.

#### Descriptive variables

Morbidity will be assessed by the primary diagnosis on admission to rehabilitation as well as the Cumulative Illness Rating Scale in its adaptation to geriatric patients (CIRS-G). This scale covers 13 somatic domains as well as one psychiatric domain [35].

Furthermore, hospital readmissions including the reasons for rehospitalization and the duration of inpatient treatment as well as the number of falls and fall-related injuries will be recorded by weekly and monthly interviews via telephone during the intervention (week 1 to 12 ± 1) and follow-up period (week 13 to 26 ± 2), respectively.

The cognitive status of the participants will be evaluated by using the Trail Making Test A + B (TMT). The TMT provides information on visual search, scanning, speed of processing, mental flexibility, and executive functions [44].

Goal Attainment will be evaluated with the Goal Attainment Scale [54] after the twelve-week training intervention (T1).

The experience with the use of smartphones, tablets, or laptops will be documented. To evaluate the usability of the telemedicine application, the System Usability Scale, a 10-item questionnaire with a 5-point Likert scale, will be used in the tablet IG [56]. The Mobile Device Proficiency Questionnaire-16 (MDPQ-16) will be used to assess basic and advanced proficiencies related to tablet and smartphone use across different subscales. The participants will be asked to rate their ability to perform 16 operations on a tablet device or a smartphone on a 5-point Likert-scale [55].

### Health economic evaluation

A cost-effectiveness analysis will be conducted after six months (T2). Intervention costs as well as health care utilization costs will be considered for the evaluation. All costs directly related to the intervention will be estimated with personnel costs based on the average German wages of the professional groups involved and their time spent on the intervention. Participants’ utilization of health-care services will be assessed with an adapted version of the FIMA questionnaire (German: ‘Fragebogen zur Inanspruchnahme medizinischer und nicht-medizinischer Versorgungsleistungen im Alter’) [37]. This questionnaire considers both medical services (e.g. inpatient and outpatient treatment, medications, rehabilitation services) as well as formal and informal care (e.g. assistance with activities of daily living by relatives, neighbors, or friends). Service use will be collected retrospectively for three months at T1 and T2. Costs will be calculated by monetary valuation of service use using standard unit costs [63]. For the cost-effectiveness analysis, health effects will be measured by quality-adjusted life years (QALYs) [64] based on the EQ-5D-5L [65]. Incremental cost-effectiveness ratios (ICER) will be calculated as the ratio between the difference in mean costs and the difference in mean effects. To account for statistical uncertainty, cost-effectiveness acceptability curves will be constructed based on net benefit regressions [66].

### Process evaluation

In order to evaluate the implementation of the GeRas program intervention and the success of continuity of care, a process evaluation will be conducted using interviews and questionnaires in health-care providers, patients, and intervention developers. The process evaluation aims to assess the intervention in terms of effectiveness, scalability, and sustainability. This process evaluation is based on the Consolidated Framework for Implementation Research, a recognized framework in implementation research [67]. It will be examined, a) whether the intervention of the GeRas program is implemented as intended (intervention fidelity), b) whether the intervention needs to be adapted (adaptation), c) to what extent the intervention of the GeRas program is implemented (dose), d) whether the potential addressees are reached (reach), and e) how participants evaluate the intervention and whether they adhere to the program (participant response). Furthermore, the experiences and perceptions of health-care providers involved in the implementation of the intervention will also be evaluated. The process evaluation will help to identify significant barriers and facilitators for successful implementation (context factors) and later transferability of the intervention into standard care (sustainability and transferability). Data will be collected based on a mixed-methods approach using a paper-based survey and semi-structured interviews. The participants will be asked to complete a brief paper-based survey and to participate in an interview after the completion of the intervention period. Health-care providers will be interviewed throughout the implementation period in order to capture early and later experiences and will be asked to complete a paper-based survey at the beginning and the end of the implementation period.

### Participant timeline

All patients will be screened for eligibility during the first two weeks after admission to inpatient GR and approached for participation if eligible. Following their informed consent, patients will be randomly assigned to one of the two IGs or the CG three to five working days before discharge. The baseline assessment will be completed within two to six working days (Monday to Friday) after discharge. The patients assigned to the intervention groups will be contacted by social workers of the health insurance after completion of the baseline assessment and no later than six days after discharge. The intervention period ends 13 weeks after discharge from GR. In order to harmonize the recording of falls and intercurrent medical events between the groups, all participants will be contacted weekly during the 13 weeks after discharge. These contacts will be conducted either as part of the scheduled contacts with the physical therapists (IGs) or through telephone calls explicitly asking about falls and medical events (CG). During the follow-up, all participants will be contacted monthly by telephone. Further assessments will be performed 3 months and 6 months after discharge. All assessments will last about 90 min each.

### Sample size

A power estimation was performed for the comparison of conventional IG vs. CG with differences in SPPB total score between T0b and T1. Information on changes within the control group and standard deviations is taken from a previous study [21]. A minimal clinically significant effect was defined as 1 point of the SPPB total score according to Perera et al. [68]. Assuming a recruitment of 90 participants in each study center will result in 270 participants in total within the recruitment period. At the study end, 182 participants (distributed among the three study groups) would be left for analyses after deducting 10% of participants due to a potentially higher variance in a multicenter design and an additional 25% due to the expected number of dropouts. This number of participants is sufficient to achieve a power of > 80% at a significance level of 5% using a 2-tailed *t*-test regarding the mentioned effect.

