### Randomization and blinding

Participants will be randomly assigned to one of the IGs or the CG using computer-generated block randomization with a 1:1:1 allocation ratio stratified by study site. The randomization will be performed by the Institute for Epidemiology and Medical Biometry of Ulm University, Ulm, Germany, using the randomization program ROM [69]. All assessments of primary and secondary outcomes will be performed by assessors blinded to group allocation. Data that reveal group allocation (e.g., training diaries) will be collected by the unblinded physical therapists prior to T1.

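### The 182 given as the analysis number is an effective sample size; the stated 25% dropout leaves about 202, and the confirmatory SPPB comparison as written appears not to use site

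*Protocol article*

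**What the plan says.** The Sample size section of the protocol article powers the conventional IG against the CG on the change in SPPB from T0b to T1. On the target effect it says: "A minimal clinically significant effect was defined as 1 point of the SPPB total score". On recruitment: "Assuming a recruitment of 90 participants in each study center will result in 270 participants in total within the recruitment period". It then gives the number expected at the end: "182 participants (distributed among the three study groups) would be left for analyses after deducting 10% of participants due to a potentially higher variance", and "an additional 25% due to the expected number of dropouts". The power statement is attached to that figure: "This number of participants is sufficient to achieve a power of" more than 80%, at a two-sided 5% level with a t-test. The SD is taken from a cited earlier study and is not printed.

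The Randomization and blinding section specifies "computer-generated block randomization with a 1:1:1 allocation ratio stratified by study site". The Statistical analyses section makes the SPPB comparison of conventional IG with CG the confirmatory one, under intention to treat. It names no test for it, and it lists further comparisons that take covariates into account among the exploratory analyses.

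**The concern.** Two reductions of different kinds are merged into one head count. Dropouts leave the dataset. A margin for higher variance does not: those patients are measured and analysed, and each simply carries somewhat less information. Calling the product the number that remains for analysis therefore understates the expected analysis set.

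This affects how the final report will be read. If about 202 are analysed, retention will look better than planned when it is exactly the assumed 25% loss. If 182 are analysed, the trial will look on plan when 1 − 182/270 = 33% have been lost. The power sentence also rests on a three-arm total, although the powered comparison uses two arms.

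The second issue is site. The design stratifies on it and the sample size makes an allowance for the multicentre setting, but the analysis as described gives site no place in the confirmatory test. When a stratification factor is related to outcome, a test that ignores it overstates the standard error and gives up some power.

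**Working it through.** **Inputs from the protocol article:** 270 recruited, 1:1:1, 10% variance deduction, 25% dropout, 1-point SPPB effect, two-sided 5%, t-test. **Assumed, because the article does not give them:** the SD, and the share of outcome variance explained by site (ρ).

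**1. The plan's figure.**
- Sequential deduction: 270 × 0.90 × 0.75 = 182.25, which reproduces 182.
- Adding the percentages: 270 × 0.65 = 175.5, which does not.
- Dropout alone: 270 × 0.75 = 202.5, which does not.

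So the 10% was subtracted as if it were people.

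**2. Head count and effective size.**

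| | Total | Per arm | Two arms |
|---|---|---|---|
| Evaluable after 25% dropout | 202.5 | 67.5 | 135 |
| Stated 182 | 182 | 60.7 | 121 |

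The 10% deduction equals a variance inflation of 1/0.9 = 1.11, or an SD inflation of √1.11 = 1.054.

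**3. What this does to power (exact two-sample t-test, 1-point effect).** The largest SD that still gives 80% power is 1.95 at 60.7 per arm and 2.06 at 67.5 per arm. These are the same requirement before and after the margin: 2.06/1.054 = 1.95. Over a range of assumed SDs:

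| Assumed SD | Power at 60.7 per arm | Power at 67.5 per arm |
|---|---|---|
| 1.75 | 87.7% | 90.9% |
| 1.90 | 82.0% | 85.9% |
| 2.00 | 78.0% | 82.2% |
| 2.25 | 68.0% | 72.7% |

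**4. Ignoring site.** With allocation balanced within sites, the true variance of the treatment difference depends on the within-site variance, a fraction (1 − ρ) of the total. The unadjusted t-test uses the total. Its standard error is too large by 1/√(1 − ρ), and its real two-sided error is 2[1 − Φ(1.96/√(1 − ρ))]:
- ρ = 2%: factor 1.010, error 4.8%
- ρ = 5%: factor 1.026, error 4.4%
- ρ = 10%: factor 1.054, error 3.9%

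A simulation (20,000 trials per setting, three equal sites, 60 per arm, assumed total SD 1.9) agrees within simulation error. At ρ = 10%, type I error was 3.9% unadjusted and 5.0% with site in the model; power was 82.8% and 85.5%. At ρ = 5%, type I error was 4.2% and 4.8%; power was 82.0% and 83.4%.

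**The case against.** The arithmetic behind 182 is correct, and the sentence names both deductions with their reasons, so a careful reader can recover 202. The section also says that the total is spread over three arms and names the two-arm comparison, so 121 can be worked out too. The direction is conservative: correcting the label raises the expected analysis set, and ignoring site holds the error rate below 5%. All of this stands, and it limits the weight of the point. It does not make 182 a count of patients available for analysis.

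On site, the t-test appears only in the power paragraph, where a simple test is a common planning device. The Statistical analyses section names no confirmatory test, and an SAP that is not shown could include site. A reader might infer that the confirmatory test definitely omits site. The article leans that way but does not establish it. The powered outcome is also a change score, in which stable site differences in SPPB level cancel, so ρ may be small.

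Two further inferences are tempting and unsupported:
- **The trial is underpowered, or the power claim is false.** The SD is not printed, so the claim can be neither confirmed nor refuted from the article.
- **The 10% allowance exists because site is left out of the test.** The text says only "after deducting 10% of participants due to a potentially higher variance in a multicenter design". That could equally mean more varied patients within sites, several assessors, or treatment effects that differ between sites, none of which a fixed site effect removes.

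**Conclusion.** The point holds as a mislabelled sample-size figure. The article's own dropout rate gives about 202 evaluable patients, 20 more than stated, with about 67 rather than 61 per arm and 135 rather than 121 in the confirmatory comparison. This part rests on the Sample size section alone and needs no assumption. The error is conservative. The claim of more than 80% power holds if the SD of the change is below about 1.95 at the effective size, or below about 2.06 on the head count.

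The site part is smaller and conditional. As written, the confirmatory comparison appears not to use the stratification factor. If that is how it is run, the cost is a slightly conservative test (real error 4.8%, 4.4% or 3.9% at assumed site shares of 2%, 5% or 10%) and a modest loss of power, 1.4 to 2.7 percentage points in the simulated settings at 5% and 10%. It does not threaten the validity of a positive result.

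**What to change.** Restate the Sample size section as: 270 randomised; about 202 evaluable after 25% dropout, that is about 67 per arm and 135 in the confirmatory comparison of conventional IG with CG; about 61 per arm as the effective size after a 10% variance margin. Attach the power statement to the per-arm effective size rather than to the three-arm total.

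Include study site as a fixed effect in the confirmatory SPPB model, or confirm that the SAP already does so, and settle this before the analysis.

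The cost is a text correction and one model term. No additional patients or data are needed.

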### Recruitment

After admission to inpatient GR, potentially eligible participants will be identified by means of a pre-screening (health insurance with AOK Baden-Württemberg, residence within the catchment area of the study site). The patients' eligibility will be further ascertained by a geriatrician according to inclusion and exclusion criteria (Table 1). If the patients are eligible and willing to participate, the geriatrician or the local study coordinator will obtain written informed consent from the patients.

### Randomization and blinding

Participants will be randomly assigned to one of the IGs or the CG using computer-generated block randomization with a 1:1:1 allocation ratio stratified by study site. The randomization will be performed by the Institute for Epidemiology and Medical Biometry of Ulm University, Ulm, Germany, using the randomization program ROM [69]. All assessments of primary and secondary outcomes will be performed by assessors blinded to group allocation. Data that reveal group allocation (e.g., training diaries) will be collected by the unblinded physical therapists prior to T1.

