The aim of this three-center study is to establish a three-month multimodal home-based intervention program following discharge from inpatient GR. The GeRas program *(“Geriatric Rehabilitation success”) *is a multi-professional intervention that includes individually adjusted progressive physical exercises, social counseling, and nutritional recommendation, initiated during the inpatient treatment and continued through a structured handover in the outpatient setting. The intervention will be delivered either conventionally by home visits and telephone calls (conventional intervention group, conventional IG) or based on an eHealth system by using tablet computers and a combination of home visits and video calls (tablet IG). The primary study aim is to evaluate the effectiveness of the GeRas program on the lower extremity function and, additionally, the social participation after three months. Secondary study aims will focus on the primary outcomes after six months, physical activity, frailty, concerns about falling, falls, movement-related self-efficacy, life-space mobility, nutritional status, health status, and health-related resource use. Furthermore, the costs and cost-effectiveness of the GeRas program will be analyzed, the tablet IG and the conventional IG compared, and barriers and facilitators for the implementation into routine care identified.

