### Content of the intervention

The following is a brief description of the individual components of the intervention.*a) Physical exercise program*

The home exercises are based on a structured program that has been evaluated previously [20]. No later than 10 days after discharge from inpatient GR, the first home visit will take place, during which the exercise program will be individually adapted and practiced. The program consists of three exercises to strengthen the lower limbs and three exercises to train the participants’ balance. Each exercise is available in three levels of difficulty to enable a progression of the training (see supplementary material). The appropriate level of difficulty is based on the participants’ goals, adapted to their individual physical abilities, and determined by the therapists. In addition, a walking course within the participants’ neighborhood is agreed upon to improve the participants’ physical endurance. The second home visit will take place the following week to review and correct any mistakes. The participants are encouraged to complete all exercises once per day. Supervision of the training program by the physical therapists is performed through a total of five home visits and weekly telephone calls (conventional IG) or two home visits, three video consultations, and weekly video calls (tablet IG). To encourage and evaluate adherence to exercise, the participants are asked to keep a training diary.

The participants of the tablet IG can see their exercises as daily tasks in their calendar view (Fig. 2). Once clicked and marked as successfully completed, the participants automatically receive motivational feedback and a small bell icon in the calendar view changes to a star icon. The tasks marked as completed allow the physical therapists to remotely monitor exercise compliance.

The difficulty of the exercises will be gradually and individually adjusted by the physical therapists as the physical capacity changes over the course of the intervention. This progress can be monitored and controlled based on the exercise completions recorded by the participants. In addition, weekly telephone or video calls are used to increase motivation and to record falls or other adverse health events.*b) Social counseling*

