### Data collection and management

A database management system (in-house developed based on TeleForm® and MS-Access®) with components both on-site at the study center and at the data management center will be used for data collection and management. For the baseline and follow-up assessments at the participants' homes, an electronic case report form with programmed plausibility checks will be used to be completed offline and later uploaded to the database. Paper-based case report forms or documents (e.g. medical discharge questionnaires, training diaries, or process evaluation questionnaires) will be used in a machine-readable format and the collected data will be integrated into the database after verification. The on-site database management system includes automatic functions for reminding data collection and detecting missing or implausible data entries. This approach minimizes errors and missing data and ensures a high quality of data collection. Individual and identifiable information of the participants will only be stored in the on-site database as well as on encrypted local servers at the respective study site. Intercurrent events (falls, adverse events) in all groups will be collected by the physical therapists, entered on the telemedicine platform, and forwarded to the database manager via the telemedicine provider. All other data entries and contents of the telemedicine platform can be integrated into the database via the same path, if required. Only authorized study personnel and the external clinical monitor will have access to the database. All pseudonymized data will be collected at the data management center and the final data set will be accessible only to study personnel directly involved in the data analysis.

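### Falls are a secondary outcome collected by unblinded therapists, and enquired about differently by arm in weeks 1 to 13, although the protocol says all secondary outcomes are assessed blinded

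*Protocol article*

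**What the plan says.** The section Randomization and blinding states: "All assessments of primary and secondary outcomes will be performed by assessors blinded to group allocation". The next sentence gives the status of the therapists: "Data that reveal group allocation (e.g., training diaries) will be collected by the unblinded physical therapists prior to T1".

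Table 2 lists "Number of falls" with code S (secondary). It is ticked at baseline (T0b), at the weekly and monthly contacts, and at the three- and six-month visits (T1, T2). The Background also names falls among the secondary aims: "Secondary study aims will focus on the primary outcomes after six months, physical activity, frailty, concerns about falling, falls".

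On who collects, Data collection and management states: "Intercurrent events (falls, adverse events) in all groups will be collected by the physical therapists".

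On how, Participant timeline gives the intention, "In order to harmonize the recording of falls and intercurrent medical events between the groups, all participants will be contacted weekly", and then the method for the intervention groups (IGs) and the control group (CG): "either as part of the scheduled contacts with the physical therapists (IGs) or through telephone calls explicitly asking about falls and medical events (CG"). Content of the intervention says of the IGs that "weekly telephone or video calls are used to increase motivation and to record falls or other adverse health events". After week 13, all participants are telephoned monthly.

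**The concern.** A reader who relies on the blinding sentence would grade the fall outcome as blinded. By the protocol's own account of data collection it is not. The person asking knows the allocation. In the IGs that person also delivers the exercise programme whose benefit and harm are being counted.

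The form of the enquiry also differs between the arms during the intervention period. Recall and reporting of falls can depend on how and in what context the question is put. A difference in capture between arms passes straight into the fall rate ratio, and a larger sample does not remove it. Falls matter twice here: they are a secondary efficacy aim of a home exercise programme, and fall-related events are the adverse events of special interest.

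**Working it through.** The protocol states no figure on this point, so the check is first a comparison of statements.

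1. Scope of the blinding sentence: all primary and secondary outcomes, without exception.
2. Status of falls: code S in Table 2 and a named secondary aim, so within that scope.
3. Could the word assessments cover only the T0b, T1 and T2 visits? Table 2 ticks falls at the weekly and monthly contacts, and its footnote calls these contacts interim assessments. In the protocol's own terms they are assessments.
4. Collector: the physical therapists, in all groups.
5. Blinding status of the therapists: unblinded.

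Statements 1, 2, 4 and 5 cannot all hold for falls.

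Mode of enquiry:

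| Period | IGs | CG |
|---|---|---|
| Weeks 1 to 13 | within scheduled therapist contacts (visit, telephone or video); the weekly calls also serve motivation | telephone call on falls and medical events |
| Follow-up | monthly telephone | monthly telephone |

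Weekly frequency is common to all arms. Mode is not, in weeks 1 to 13 only.

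Intercurrent medical events are coded D (descriptive) in Table 2. They share the collector and the difference in framing, but the blinding sentence does not cover them.

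To show what differential capture could do, take a true rate ratio of 1 and let one arm's falls be captured at a fraction s of the other's. The observed rate ratio is then s. For the chance of a false finding in a two-sided 5% Wald test on the log rate ratio:

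- Number per arm: 270 × 0.90 × 0.75 = 182.25, which reproduces the protocol's 182; 182/3 is about 61.
- Assumed, not from the document: negative binomial counts with dispersion k = 1, and a mean μ of 0.3, 0.6 or 1.0 falls per person in three months.
- Variance of the log rate in an arm: (1/μ + k)/61.

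Example with μ = 0.6 and s = 0.8. The captured means are 0.48 and 0.60. The variances are (1/0.48 + 1)/61 = 0.0505 and (1/0.60 + 1)/61 = 0.0437, so SE = √0.0942 = 0.307. Then ln(0.8)/SE = −0.223/0.307 = −0.727, and the chance of rejection is Φ(−1.96 + 0.727) + Φ(−1.96 − 0.727) = 0.112.

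| Relative capture s | Observed rate ratio | μ = 0.3 | μ = 0.6 | μ = 1.0 |
|---|---|---|---|---|
| 100% | 1.00 | 5.0% | 5.0% | 5.0% |
| 90% | 0.90 | 5.9% | 6.4% | 6.9% |
| 80% | 0.80 | 8.7% | 11.2% | 13.5% |
| 70% | 0.70 | 14.2% | 20.5% | 26.3% |

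If the CG is the arm with lower capture, the ratios invert (1/0.9 = 1.11, 1/0.8 = 1.25).

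**The case against.** The best defence is that much is already aligned: the same weekly frequency, the same profession collecting in all groups, one set of fall details and one severity classification (Data and safety monitoring), and a common monthly telephone call after week 13. Recording falls is a stated purpose of the IG calls, not an afterthought. Falls are one of many exploratory endpoints. A condensed article need not print a question script, so one may exist. All of this stands. It limits the size of the concern, but it does not reconcile the blinding sentence with therapist collection, and it does not make the described mode the same in weeks 1 to 13.

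The section Descriptive variables also lists number of falls, recorded by telephone interview. If falls are only descriptive, the blinding sentence does not reach them. But that conflicts with code S in Table 2 and with the secondary aims, and so adds a second inconsistency to settle.

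A reader might infer several stronger things that the text does not support:

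- That the dedicated CG call finds more falls, so that the IGs will look better. Nothing in the document fixes the direction; weekly coaching could equally prompt more reporting.
- That adverse events contradict the blinding sentence. They are coded D and lie outside it.
- That IG-only training diaries, ticked at T2, will unblind the T2 assessor. The document does not say who collects them at T2, and an unstated route is not a leak.
- That a blinded fall count exists at T1 and T2. Table 2 ticks the item at those visits but names no collector, while Data collection and management names the therapists.

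**Conclusion.** The contradiction is firm and rests on the text alone: falls, coded as a secondary outcome, are collected by unblinded staff although the protocol says that all secondary outcomes are assessed blinded. The difference in mode is equally explicit but confined to weeks 1 to 13.

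The consequence is a risk of ascertainment bias in the exploratory fall comparison, not a demonstrated bias. The observed ratios of 0.90 or 0.80, and the false-finding rates of about 6 to 7% and 9 to 14%, hold only under the assumed relative capture of 90% or 80% and the other inputs listed. The comparison of adverse and medical events carries the same risk without the contradiction. The confirmatory comparison of conventional IG with CG is unaffected. The point is worth correcting because the correction is cheap and a stated design property is missing for one named outcome.

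**What to change.** 1. Except falls from the blinding sentence, and report the fall outcome as collected unblinded.
2. Reconcile the S code in Table 2 and the secondary aims with the listing of falls under Descriptive variables.
3. Use one standard fall and event question set at every weekly and monthly contact in all three arms, asked before any other topic. If such a set already exists, say so.
4. If the set is new, introduce it on the same day in all arms and record that date.
5. If the sponsor confirms that the falls item at T1 and T2 is asked by the blinded assessor, name that count as a sensitivity analysis. If not, omit this step.

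The cost is a corrected sentence, a short question set and at most one extra analysis, with no added visits or staff. There is one small downside: 122 of 270 participants (45%) were enrolled by August 2023, so a new set creates two ascertainment periods. Because allocation is in blocks at 1:1:1, the arms should be spread similarly over the two periods, and the recorded date lets the analysis show them separately.
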